### Breaking of the Study Blind

#### On Study

In a medical emergency, when management of a participant's condition requires knowledge of the investigational product, the randomisation code may be broken to determine the treatment allocation of the participant. If this is required the investigator can contact the pharmacy to obtain the treatment identity. If possible, such emergencies will be discussed with the Principal Investigator before disclosure of the treatment allocation (or as soon as possible thereafter). Reasons for breaking a code must be clearly explained and justified on the participant's CRF. The date on which the code is broken together with the identity of the person(s) responsible for requesting the code to be broken will also be documented.

#### Following Completion of the Study

Study unblinding will only take place once the Statistical Analysis Plan has been agreed by the trial team and after the final database has been locked. This will be achieved by obtaining the schedule linking Randomisation Numbers with the administered treatment from CEBU.

### Study Procedure

#### Dose and administration schedule

The single dose of study drug will be administered at time 0 as outlined in Study Flow Chart (Figure 1). The amount of fluid ingested within 30 and 60 minutes will be recorded on a Fluid Balance Chart.

**Figure 1 F1:**
[figure not shown]
**Study Flow Chart**. The schedule of study observations that will be recorded during the 60 minute study period and the 30 minute observation period. (legend) ED emergency department

After the end of the 60 minute fluid trial and once the outcome data has been collected, the treating clinician will complete a fluid assessment on the participant. At this point, if the treating clinician feels that a participant has not had enough fluid, he/she may decide to:

• Administer the second bottle allocated to that participant (Bottle B) - participants previously given placebo will receive the active drug (i.e. 2% viscous lidocaine), and vice versa, and/or

• Administer other oral analgesia e.g. paracetamol or ibuprofen

The study will terminate at 90 minutes (i.e. 30 minutes after the end of the 60 minute fluid trial for assessment of adverse events) where the participant will be reviewed for signs of aspiration. However, if at any point during the trial the participant starts coughing and/or show other signs of aspiration, he/she will be urgently reviewed by the treating clinician. A completed participant is one who has had the solution administered, and has had their fluid intake monitored for a minimum of 60 minutes from the time of administration of the study mixture. If the participant does not complete the 60 minute study period, the reason for the premature termination will be documented on the CRF. After the completion of the 60 minute trial of fluids routine care will follow as directed by the treating clinician.

Complications recorded will include: allergic reactions (including anaphylaxis), seizures, cardiac arrhythmia, and clinical episodes of aspiration.

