### Patient Randomisation

Patients who fulfil the eligibility criteria and whose parents provide informed consent will be randomised to either 2% viscous lidocaine or placebo.

The randomisation schedule will be computer generated using block randomisation by the Clinical Biostatistics and Epidemiology Unit (CEBU, Murdoch Children's Research Institute, Melbourne, Australia). Random block sizes will be used. The randomisation will not be stratified. Sequentially numbered bottles of either lidocaine or placebo will be arranged according to this schedule by a study pharmacist. Once a patient has been randomised they will be given the next available study number which will equate to an allocation of study drug dispensed in two bottles (labelled Bottle A and Bottle B).

At the time of randomisation patients will be given a dose of study solution from Bottle A which will contain the study drug according to their random allocation. Bottle B will contain the alternative mixture i.e. lidocaine if randomised to placebo and placebo if randomised to lidocaine. After 60 minutes the treating clinician may prescribe a dose from this second bottle if clinically warranted. This ensures that all participants in the study have access to the active treatment.

All study drugs will be packaged in blinded containers stored in a locked cupboard labelled only with the study details and the study number. Only the study pharmacist will be aware of the treatment allocation.

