#### Longer term

(1) incidence of adverse events (seizures, cardiac arrhythmias and aspiration) within the 90 minute study period; (2) the proportion of subjects who require fluid administration via intravenous line or nasogastric tube (oral hydration failures); (3) the proportion of subjects requiring hospital admission; (4) duration of stay in the ED

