### Adverse experiences

All adverse experiences either observed by the investigator or one of the clinical staff, or reported by the patient's parents/guardians spontaneously or in response to a direct question, that occur during the 60 minute study period, and the 30 minute observation period, will be evaluated by the investigator and noted in the adverse experience section of the patient's CRF. Events after the study period also thought to be due to a study intervention will be included.

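### The adverse-event window closes 90 minutes after Bottle A even when Bottle B is given late, so any delay in Bottle B shortens the observation that follows it (minor)

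*Protocol article*

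**What the plan says.** Under Study Procedure, time 0 is the single Bottle A dose. After a 60-minute fluid trial comes a further half hour for safety: "The study will terminate at 90 minutes (i.e. 30 minutes after the end of the 60 minute fluid trial for assessment of adverse events". The child is reviewed for aspiration at that point. The Figure 1 legend describes the same two periods: "The schedule of study observations that will be recorded during the 60 minute study period and the 30 minute observation period". The longer-term outcome uses the same clock: "incidence of adverse events (seizures, cardiac arrhythmias and aspiration) within the 90 minute study period". The Adverse experiences section records events over the same 60 plus 30 minutes and adds: "Events after the study period also thought to be due to a study intervention will be included".

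Patient Randomisation provides the crossover dose: "After 60 minutes the treating clinician may prescribe a dose from this second bottle if clinically warranted". Bottle B holds whichever mixture Bottle A did not. Study Procedure places two steps before it: "once the outcome data has been collected, the treating clinician will complete a fluid assessment on the participant". Neither section gives a latest time for Bottle B, and nothing in the text restarts or extends the window once it is given.

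**The concern.** The 30-minute safety period is tied to the Bottle A clock and not to the last study dose. For a lidocaine-arm child this is harmless: the lidocaine was given at time 0 and Bottle B is placebo. For a placebo-arm child the study lidocaine comes after minute 60, and only what remains of the last 30 minutes is planned observation. Children given Bottle B are those judged not to have drunk enough, and they receive it so that they will drink. The closing aspiration check could then fall while the mouth is still numb. Two things are at stake: a safety check at a useful time, and the completeness of a descriptive count of seizures, arrhythmias and aspiration.

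**Working it through.** **Inputs**
- End of study and of the adverse-event window: 60 + 30 = 90 minutes after Bottle A (Study Procedure; same window under Longer term and Adverse experiences).
- Earliest Bottle B time: after minute 60, following outcome data collection and a fluid assessment (Patient Randomisation; Study Procedure). Latest time: none stated.
- Lidocaine onset about 5 minutes; anaesthesia lasting 20 to 30 minutes (Background).
- Dose 0.15 ml/kg of a 2% mixture; recommended maximum 3 mg/kg (Background; Randomised treatments).
- Children still to be enrolled: 80 (Abstract; Time plan).
- Delay *d* from minute 60 to the Bottle B dose: not given, so the values below are assumptions.

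**Planned observation after Bottle B** = 90 − (60 + *d*) = 30 − *d* minutes. If the window instead ran at least 30 minutes from Bottle B, it would end at 60 + *d* + 30 = 90 + *d* minutes, which is *d* minutes later than now.

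| Assumed delay *d* (min) | Observation now, 30 − *d* (min) | End of window if tied to Bottle B, 90 + *d* (min) |
|---|---|---|
| 0 | 30 | 90 |
| 5 | 25 | 95 |
| 10 | 20 | 100 |
| 20 | 10 | 110 |
| 30 | 0 | 120 |

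**Against the stated duration of anaesthesia, counted from dosing (20 to 30 minutes).** The gap is the end of effect minus (30 − *d*); a positive value means that the review comes before the effect has ended.
- *d* = 0: 20 − 30 = −10 to 30 − 30 = 0. The review is not early.
- *d* = 5: 20 − 25 = −5 to 30 − 25 = +5. At most 5 minutes early.
- *d* = 10: 20 − 20 = 0 to 30 − 20 = +10. Up to 10 minutes early.

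If duration is counted from onset, the effect ends 5 + 20 = 25 to 5 + 30 = 35 minutes after the dose, and each gap rises by 5 minutes. The article does not say which reading applies.

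**Dose.** 0.15 ml/kg × 20 mg/ml = 3 mg/kg, equal to the recommended maximum and not above it.

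**Children concerned.** With equal allocation assumed, at most 80 / 2 = 40 placebo-arm children among those still to be enrolled, and fewer once recruitment is under way. The share who will need Bottle B is not stated.

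**The case against.** The strongest reply is that the plan is consistent and already follows Bottle B. Every section gives the same 60 plus 30 minutes, and the Bottle B decision is placed at the end of the fluid trial, just before the half hour kept for adverse events. For a child dosed promptly, the 90-minute review is itself a scheduled check after Bottle B, and 30 minutes equals the longest anaesthesia duration quoted. All of this stands for a prompt dose. It does not help a delayed one: two steps precede Bottle B, no latest time is set, and each minute of delay comes off the plan's own half hour.

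Other provisions also reduce the risk. Aspiration signs trigger a prompt review: "if at any point during the trial the participant starts coughing and/or show other signs of aspiration, he/she will be urgently reviewed". Ordinary care continues: "After the completion of the 60 minute trial of fluids routine care will follow as directed by the treating clinician". Later events attributed to a study intervention are included, and serious events are followed to resolution. These are real safeguards, but the first needs visible signs during the trial, the attribution clause needs a causal judgement, and none moves the scheduled review.

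A reader might infer more than the text supports:
- *That 30 minutes is too short and 35 or more is required.* The documents set no observation time after lidocaine. The figure of 35 comes from adding onset to the longest duration. It also concerns numbness, which is not tied in the documents to a risk period for seizure or arrhythmia.
- *That Bottle B is a placebo-arm child's first lidocaine of the illness.* Table 1 excludes only more than one earlier dose, so Bottle B is the first study dose.
- *That no other review exists.* Figure 1 is not shown and the article condenses a fuller protocol. The claim here covers only what the text states.

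**Conclusion.** The point holds as a minor, cheap improvement. As written, planned observation after Bottle B is 30 minutes minus the delay. That is enough for a prompt dose on the from-dosing reading, and shorter minute for minute otherwise. Events after minute 90 enter the count only through attribution.

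The actual loss depends on two unknowns, the delay and the share of children given Bottle B, so the tabulated delays are illustrations and not estimates. Expected harm is low: the Background reports adverse events only above recommended doses. A reader might also infer that a treatment comparison is compromised. It is not: the primary outcome and the short-term secondary outcomes close at 60 minutes, and the longer-term outcomes are to be described without comparing the groups.

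**What to change.** For any child given Bottle B, record the time of that dose. Run the adverse-event window and the closing aspiration review to 90 minutes after Bottle A or at least 30 minutes after Bottle B, whichever is later. Apply the rule in both arms so that a longer stay does not reveal the allocation. Use the same wording in Study Procedure, the longer-term outcome and Adverse experiences. A 35-minute minimum is optional if the team counts duration from onset; the window would then end at 60 + *d* + 35 = 95 + *d* minutes.

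The cost is a short amendment, one recorded time, and extra emergency department observation equal to the delay (the delay plus 5 minutes under the 35-minute option). It falls only on children given Bottle B, at most the 80 still to be enrolled. The 60-minute efficacy window stays as it is.

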### Outcome measures

*The primary outcome *is the amount of fluid ingested by each child, expressed in ml/kg, within 60 minutes from the time of administration of the study mixture.

### *The secondary outcome *measures are in 2 groups

#### Short term

those within 60 minutes - and longer term - those between 60 and 90 minutes. Comparisons between groups will only be made in the short term outcomes since both groups will have access to lidoocaine after 60 minutes.

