### Sample size, power and statistical methods

There is currently no published literature on the effectiveness of 2% viscous lidocaine for improving oral fluid intake in painful infectious mouth conditions, hence we carried out a pilot study of 20 patients to document the mean fluid intake and spread of the data.

The data from the pilot study found a mean difference of 4.3 mls/kg (standard deviation = 7 mls/kg) ingested over a 60 minute period between the two treatment groups. Assuming a slightly conservative estimate of the treatment effect of 4 mls/kg (standard deviation = 7), would require a sample size of 50 children per group (100 children in total), based on 80% power and 5% significance. A review of expert clinical opinion (10 paediatric emergency attendings in Melbourne, Australia) concluded that a difference of 4-5 mls/kg represented a clinically important difference.

Based on the recruitment rate in the pilot study (20 participants in 5 months) we expect patient recruitment to take 2 years (the 20 patients from the pilot study will be included in the final analysis). We have not allowed for any loss-to-follow up in this time line as we expect to retain all patients for the 60 minutes needed for the study.

Analysis will be by intention to treat. Data will be analysed descriptively and statistically using the STATA data analysis program. Data for the primary outcome will be reported with an estimate of the difference in means and its 95% confidence interval - obtained using an unadjusted linear regression. Since this is an RCT, and the outcome measure is measured on a continuous scale, the t-test will be used to compare the 2 groups. If necessary due to skewed data, the data will be log-transformed. Secondary outcomes in the short term group will be analysed with t-tests for continuous data and chi-squared tests for categorical data, while the longer term group will have descriptive statistics only. As a sensitivity analysis, all treatment comparisons for primary and secondary outcomes will also be presented adjusted for age at presentation to account for any chance imbalance between the treatment groups with respect to this potentially confounding factor using linear and logistic regression models for continuous and binary outcomes respectively.

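### Later lidocaine access does not justify leaving the longer-term outcomes without a between-arm estimate, and the reason cannot apply to adverse events in the first 60 minutes

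*Protocol article*

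**What the plan says.** The text on secondary outcomes in the protocol article divides them into short term (within 60 minutes) and longer term (60 to 90 minutes). It then rules that "Comparisons between groups will only be made in the short term outcomes", the reason being "since both groups will have access to lidoocaine after 60 minutes". The section on sample size, power and statistical methods repeats the rule: short-term outcomes are tested, "while the longer term group will have descriptive statistics only". The same section says "Analysis will be by intention to treat".

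The longer-term list has four items: adverse events over the whole 90 minutes, intravenous or nasogastric fluids, "the proportion of subjects requiring hospital admission", and length of ED stay.

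On later access, the section on patient randomisation says "After 60 minutes the treating clinician may prescribe a dose from this second bottle if clinically warranted". Bottle B holds the mixture that the child did not receive first. The study procedure ties its use to the clinician's view, at 60 minutes, that the child has not had enough fluid. Clinicians are blinded throughout.

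**The concern.** The rule rests on one reason, and that reason does not fit the outcomes it covers.

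- **Adverse events.** They are counted from time 0, so the longer-term group includes the first hour, when no child has had access to Bottle B. In that hour the comparison is simply lidocaine against placebo.
- **Fluids, admission and ED stay.** Bottle B is an optional event after randomisation, and the first treatment can influence whether it is used. Analysing children in the arm to which they were randomised remains a fair comparison of two starting strategies.

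The Background names admission for intravenous or nasogastric fluids as the risk when intake cannot be improved. As written, these outcomes would be described with no planned difference or interval. Any reader who sets the arms side by side would have no prespecified measure of uncertainty. For adverse events, a 90-minute total by arm could also count an event that followed lidocaine from Bottle B against the placebo arm.

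**Working it through.** **1. The plan's own size.** Inputs from the sample size section: difference 4 ml/kg, SD 7, 80% power, 5% significance (two-sided assumed). The normal approximation, n = 2(1.96 + 0.84)² × 7²/4², gives 49 per arm after rounding up. The t-based solution is 49.05, which rounds up to the stated 50. So 50 per arm is used below.

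**2. Does the reason fit each outcome?**

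| Outcome in the longer-term list | Can Bottle B precede it? | Does the stated reason apply? |
|---|---|---|
| Adverse events, 0–60 min | No | No |
| Adverse events, after 60 min | Yes | Affects attribution |
| Intravenous or nasogastric fluids | Yes | Affects meaning, not validity |
| Admission | Yes | Affects meaning, not validity |
| ED stay | Yes | Affects meaning, not validity |

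**3. Validity.** If lidocaine has no effect, the contents of either bottle make no difference and the arms have the same event rate. A simulated two-sided 5% test of two proportions with 50 per arm rejected in 4.6%, 5.4% and 5.1% of runs at event rates of 8%, 20% and 40%. This covers the no-effect case only.

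**4. Direction if lidocaine works.** Suppose, for illustration, that every child short of fluid at 60 minutes gets Bottle B and that only these children are admitted. Let f be the share short of fluid at 60 minutes, and r the admission risk among them after Bottle B.

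- Lidocaine first: risk = f(L) × r(placebo in Bottle B)
- Placebo first: risk = f(P) × r(lidocaine in Bottle B)

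An effective drug makes f(L) smaller than f(P), which favours lidocaine first. It also tends to make r(lidocaine in Bottle B) the smaller of the two, which favours placebo first. The sign of the difference is not determined. The Background puts the duration of anaesthesia at 20 to 30 minutes, so the first dose would no longer be acting when Bottle B is given.

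**5. Precision.** Half-width of a 95% interval for a risk difference, with the same rate p in both arms:

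1.96 × √(2p(1 − p)/50)

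| p | Source | Half-width |
|---|---|---|
| 0.08 | Background, 3 of 36 | 10.6 points |
| 0.20 | Assumed | 15.7 points |
| 0.30 | Assumed | 18.0 points |

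For ED stay: 1.96 × √(2/50) = 0.39 SD.

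**6. What a test could do.** At 8%, 0.08 × 50 = 4 events are expected per arm. Power to detect a halving from 8% to 4% is about 13%, and 553 per arm would be needed for 80%. If later lidocaine restored half the benefit in the placebo-first arm (an assumption), power would be about 7%.

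**The case against.** The strongest defence is that the restriction is prespecified and reasoned. The study aim is intake within 60 minutes, and the trial is sized on that. The strategy contrast answers a different question. It could mislead, because after 60 minutes the placebo-first children who are short of fluid may receive the active drug while their lidocaine-first counterparts may receive placebo. Other oral analgesia may also be given then. A confidence interval measures sampling error and says nothing about that problem. Admission events may be few, and descriptive reporting of rare safety events is ordinary practice.

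Most of this stands. It is why the estimates should carry an exploratory label and no significance claim. It does not rescue the reason for adverse events before 60 minutes, and it does not make the comparison by randomised arm invalid for the rest.

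Three stronger readings are tempting, and the document does not support them:

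- A reader might infer that later access can only pull the difference towards zero. Because Bottle B holds the opposite mixture, the difference could also change sign.
- A reader might infer that randomised evidence on admission and fluids is lost. The outcomes are still collected and described. If counts are tabulated by arm, anyone can compute a difference and interval. What is missing is a planned and properly labelled estimate.
- A reader might infer that the intention-to-treat statement contradicts the restriction. It governs the comparisons that are made and does not require every outcome to be compared. It does show that the plan already accepts analysis by allocation despite later treatment.

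**Conclusion.** The concern holds as a modest, inexpensive improvement. The stated reason is wrong for adverse events in the first 60 minutes. For fluids, admission and ED stay it is a reason to name the contrast carefully, not to withhold an estimate.

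The estimates would be imprecise: about ±11 points at the 8% rate and ±16 to 18 points at 20% to 30%. The 8% comes from a cited series of herpetic gingivostomatitis and may not match this broader population; the higher rates are assumptions. At 8% the half-width exceeds the event rate, so the interval would exclude only large differences. The primary outcome, its error rate and the sample size are untouched.

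**What to change.** Amend the secondary-outcome text and the matching sentence in the statistical methods as follows.

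1. Report adverse events by arm for 0–60 minutes separately from those after 60 minutes. Show the later ones also by whether Bottle B was given.
2. Report intravenous or nasogastric fluids, admission and ED stay by randomised arm, each with a difference and 95% confidence interval. Describe the contrast as initial lidocaine versus initial placebo, with optional blinded access to the other mixture after 60 minutes. Label it exploratory, make no significance claim, and state that it is not lidocaine versus no lidocaine.
3. Print the number given Bottle B in each arm beside these results.

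The cost is a few lines of wording and code. No new outcome is needed, provided the case report form records the time of each adverse event and whether Bottle B was given, which is assumed here. The downside is a set of imprecise estimates that need a caution in the report.
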